#### 2.3.4 Diagnosis of targeted diseases (conditions)

The diseases to be analyzed in this study include AAD, OA, and FAOD, which are detected by measuring acylcarnitines, succinylacetone, and amino acids with MS/MS. For their diagnosis, the ratios of Phe/Tyr, C3/Met, C3/C2, C3/C0, С14:1/С2, С14:1/С16, С14:1/С12:1, С0/(С16+С18), and (C14 + C14:1 + C16:1)/C0 will be set. IEMs subject to diagnosis are displayed in Table 3. Limit values will be determined by studying levels of amino acids, acylcarnitines, and succinylacetone in DBSs of 750 healthy children in western Kazakhstan. In the case of normally distributed data, the cut-offs will be set to four standard deviations (SD) above or below the mean. If the distribution of analytes is skewed, reference intervals in the healthy control group will be determined nonparametrically and correspond to the 2.5–97.5th percentile of the experimental distribution. All cut-offs are subject to adjustment in light of further analyzes and additional clinical data.

**TABLE 3 T3:** Primary and repeated LC-MS/MS screening and confirmatory IEM tests.

Disorder	Primary and repeated LC-MS/MS screening	Confirmatory tests
AMINO ACIDS & UREA CYCLE DISORDERS		
PKU	↑Phe, ↑Phe/Tyr ratio	↑Phe, Phe/Tyr ratio (Blood)
		↑Phenyl acetic acid (Urine)
		Genetic sequencing of the PAH gene
MSUD	↑Val, Ile, Leu	↑Val, Ile, Leu (Blood)
	↑ Leu/Ile	↑Val, Leu/Ile, Leu/Phe ratio (Blood)
	↑Leu/Phe	↑α-KG, 2OH-IVA (Urine)
	↑Xle/Ala	Genetic sequencing of the BCKDHA, BCKDHB genes
	↑Xle/Phe	
	↑Val/Phe ratio	
HCU	↑Met, Hcy	↑Met, Hcy (Blood)
	↑Met/phe ratio	
CIT I	↑Cit	↑Cit (Blood)
		↑OA (Urine)
		Genetic sequencing of the ASS1 gene
ASA	↑Argininosuccinic acid	↑Argininosuccinic acid (Blood)
		↑Argininosuccinic acid (Urine)
		Genetic sequencing of the ASL gene
OTCD	↓Cit ↑Orn	↓Cit (Blood)
		↑ Glu (Blood)
		↑Orotic acid (Urine)
		Genetic sequencing of the OTC gene
CPS	↓Cit	↑Organic acids (Urine)
		Genetic sequencing of the CPSI gene
NAGSD	↓Cit	↓Cit (Blood)
		Genetic sequencing of the NAGS gene
TYR I	↑Tyr ↑Tyr/Phe ratio	↑ Cit (Blood)
		↑ SuAc (Urine)
		↑ OA (Urine)
		Genetic sequencing of the FAH gene
TYR II	↑Tyr	Normal levels succinylacetone (Urine)
		Genetic sequencing of the TAT gene
NKHG	↑Gly	↑Gly (Blood)
		↑Gly (CSF/P)
ARG	High arginine ↑Arg/Orn	High plasma arginine and high urinary orotic acid
ORGANIC ACID DISORDERS		
SBCAD	↑С5	Genetic sequencing of the ACADSB gene
MMA	↑C3	↑C3, C3/C2 ratio (Blood)
	↑C3/C2 ratio	↑MMA, 3OH-PA, MCA, PG (Urine)
	↑C4DC, C3/C0	
PA	↑C3	↑Gly (Blood)
	↑C3/C2 ratio	↑C3, C3/C2 ratio (Blood)
	↑C3/C0 ratio	↑3OH-PA, MCA, PG (Urine)
		Genetic sequencing of the PCCA, PCCB genes
IVA	↑C5	↑C5 (Blood)
	↑C5/C2 ratio	↑IVG isovalerylglycine, ↑ 3OH-IVA (Urine)
	↑ C3/C2 ratio	Genetic sequencing of the IVD gene
IBDD	↑С4	↑С4 (Blood)
		Genetic sequencing of the ACAD8 gene
GA I	↑C5DC	↑C5-DC (Blood))
	↑C5DC/C8 ratio	↑GA, 3OH-GA (Urine)
		Genetic sequencing of the GCDH gene
3MCCD	↑C5-OH	↑C5-OH (Blood)
		↑3OH-IVA, 3MCG (Urine)
MCD, MCC	↑C3, C5-OH	↑C3, C5-OH (Blood)
		↑C3, C5-OH (Urine)
		Genetic sequencing of the HLCS gene
BTD	↑C5OH	↓Biotinidase activity (Blood) Genetic sequencing of the BTD gene
MA	↑C3DC	↑C3DC (Urine)
	↑C3DC/C4 ratio	Genetic sequencing of the MLYCD gene
MATD	↑C5:1, C5-OH	↑ C5:1, C5-OH (Blood)
		↑ TGL (tiglylglycine), 2methyl-3OH butyric (Urine)
		Genetic sequencing of the ACAT1 gene
MHBDD	↑C5	Genetic sequencing of the ACADSB gene
3HMG	↑ C5-OH	Genetic sequencing of the HMGCL gene
	↑C 5OH/C3	
	↑C6DC	
3MGA	↑C5-OH	↑C5-OH (Blood)
	↑С6DC	↑3OH-IVA, 3MGA (Urine)
		Genetic sequencing of the AUH gene
FATTY ACID OXIDATION DISORDERS		
MCAD	↑C6, C8, C10	↑n-hexanoylglycine and 3-phenylpropionylglycine (Urine) Genetic sequencing of the ACADM gene
	↑C8/C10 ratio	
	↑C10:1 ratio	
	↑ C8/C2 ratio	
VLCAD	↑C12, C14, C14:1, C16, C16:1, C18:1	Genetic sequencing of the ACADVL gene
	↑С14:1/С2 ratio	
	↑С14:1/С12:1 ratio	
	↑C14:1/C16 ratio	
SCAD	↑C3, C4, C6	↑Ethylmalonic acid (EMA) (Urine) Genetic sequencing of the ACADS gene
	↑C4	
	↑C4/C2	
LCHAD	↑C16OH	Genetic sequencing of the HADHA gene
	↑ С16OH	
	↑C18OH	
	↑C18:1OH	
MADD (GA II)	↑C4, C5, C5-OH, C5-DC, C6, C8, C14, C16, C12	↑C4, C5, C5-OH, C5-DC, C6, C8 (Blood)
		↑GA, EMA, C4–C8 AGs, isovalerylglycine (Urine)
		Genetic sequencing of ETFA, ETFB, ETFDH genes
CUD	↓C0	↓C0 (Blood)
	↓long-chain acylcarnitines	↓C0 (Urine)
		Genetic sequencing of the SLC22A5 gene
CPT I	↑C0, ↑C0/C16 + C18 ratio	↑C0 (Blood))
	↓C16, C18, С18:1, С18:2	↑C0/C16 + C18 (Blood)
		Genetic sequencing of CPT1A, CPT1B, CPT1C genes
CPT II	↓C0	Genetic sequencing of the CPT2 gene
	↑C14, C16, C16:1, C18, C18:1, С18:2	
CACT	↓C0	Genetic sequencing of the SLC25A20 gene
	↑C16, C18, C18:1, С18:2	
DE RED	↑С10:2	Genetic sequencing of the DECR1 gene
MCAT	↑C6-OH	
	↑C8	
	↑С10:1ОН	

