### 3.2 Statistical analysis

Shapiro-Wilk and Kolmogorov-Smirnov tests will be used to check the normality of the distribution. As a rule, the distribution of free carnitine and acylcarnitines concentrations in whole blood differs from normal (Manta-Vogli et al., 2020). If the data sets show a normal distribution, M (mean) and standard deviation (error of the mean) will be used for descriptive statistics of the samples. Parametric tests will be used to test for differences between AA and AC concentrations depending on various factors (gender, place of residence) (t-test, analysis of variance (ANOVA) with or without Tukey’s test). If the data sets do not show a normal distribution, Me (median) and quartiles (interquartile range IQR) will be used for the descriptive statistics of the samples. Non-parametric tests (Mann-Whitney U-test, Kruskal-Wallis H-test without or with subsequent *post hoc* comparisons using U-test will be applied to test the differences mentioned above. The Pearson χ^2^ criterion will be applied to identify intergroup differences for categorical variables. If the distribution of analytes is skewed, reference intervals in the healthy control group will be determined nonparametrically and correspond to the 0.5–99.5th percentile of the experimental distribution. Correlations between body weight, and concentration of each analyte will be performed using corresponding tests.

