#### 3.2.1 Descriptive statistics and group comparison

Descriptive statistics and reference intervals for whole blood concentrations of 15 AAs, 35 ACs, and SuAc in healthy children divided into subgroups according to gender will be presented in tables. For each analyte in the healthy control group, the upper cut-off will be set above the 97.5^th^ percentile, while the lower cut-off will be set below the 2.5th percentile. Differences in the distribution of amino acids, acylcarnitines, and succinylacetone between groups, as determined using the Mann-Whitney and Kruskal-Wallis tests, will be noted in the table if found.

Cut-off values for analytes and their ratios for selective screening of AAD, OA, and FAOD presented in Table 3 will be pointed out. The results of determining the analytes in DBS in children of the healthy control group will be compared with those of previously published studies in other populations. According to the inclusion criteria, healthy newborns in the reference group must be full-term (born at 37–42 weeks). However, it should be taken into account that some of the newborns at risk for IEM are born prematurely. In this regard, it is also necessary to determine reference intervals for the concentrations of 15 AAs, 35 ACs and SuAc in dried blood spots of premature infants who do not have clinical symptoms of IEM.

Comparison of mean concentrations (Me, range) of analytes between groups of high-risk children and healthy controls will be presented.

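### The mean − 4 SD lower cut-off in section 2.3.4 is zero or negative once the CV reaches 25%, so low citrulline could not be flagged if citrulline tests as normal with that spread

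*Protocol article*

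**What the plan says.** Section 2.3.4 derives the limits from the reference group: "Limit values will be determined by studying levels of amino acids, acylcarnitines, and succinylacetone in DBSs of 750 healthy children". It then splits by distribution. For normal analytes: "In the case of normally distributed data, the cut-offs will be set to four standard deviations (SD) above or below the mean". For skewed analytes, the reference intervals are "determined nonparametrically and correspond to the 2.5–97.5th percentile of the experimental distribution". The same section leaves every cut-off open to later adjustment.

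Other sections give different rules:

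- Section 3.2 repeats the skewed-data rule with other limits: "determined nonparametrically and correspond to the 0.5–99.5th percentile of the experimental distribution".
- Section 3.2.1 covers each analyte with no condition on distribution, "while the lower cut-off will be set below the 2.5th percentile".
- Section 2.3.1 takes cut-offs from the kit manual and adjusts them as samples accumulate.

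On choosing the branch, section 3.2 says "Shapiro-Wilk and Kolmogorov-Smirnov tests will be used to check the normality of the distribution", and also "As a rule, the distribution of free carnitine and acylcarnitines concentrations in whole blood differs from normal".

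Table 3 has 37 disorder rows (12 + 14 + 11). Seven of them use a low value as a primary screening marker:

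- Low citrulline: OTCD (with raised ornithine), CPS (alone) and NAGSD (alone).
- Low free carnitine: CUD (with low "long-chain acylcarnitines"), and CPT II and CACT (each with raised long-chain acylcarnitines).
- Low C16, C18, C18:1 and C18:2: CPT I (with raised free carnitine and a raised ratio).

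**The concern.** The 4 SD rule treats the two tails alike, but a concentration in µmol/L is bounded at zero. With a wide enough spread the lower limit reaches that bound, and a low result then cannot be abnormal however depleted the child is. With a somewhat smaller spread the limit is positive but so low that it flags only extreme depletion.

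Later steps do not make up for this. Under section 2.3.5, referral for confirmatory testing follows from a result beyond its threshold. A child whose only primary marker cannot cross its limit is therefore not sent to sequencing by this route. The disorder frequencies feed tasks 1 and 3, and the Discussion ties the choice of conditions for a future national panel to them.

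**Working it through.** **Inputs.** The multiplier 4 is from 2.3.4. The percentiles are 2.5 (2.3.4 and 3.2.1) and 0.5 (3.2). There are 750 healthy and 1,500 screened children. The article states no mean, SD, CV or numerical cut-off for any analyte, so there is no figure to reproduce, and the CV is shown as a range.

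**Step 1: the lower limit as a share of the healthy mean.** With CV = SD/mean, (mean − 4 SD)/mean = 1 − 4 CV. This is zero or negative exactly when CV ≥ 1/4. For comparison, the normal-theory percentiles are 1 − 1.960 CV (2.5th) and 1 − 2.576 CV (0.5th).

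| CV (assumed) | mean − 4 SD | 2.5th percentile | 0.5th percentile |
|---|---|---|---|
| 15% | 0.400 | 0.706 | 0.614 |
| 20% | 0.200 | 0.608 | 0.485 |
| 24% | 0.040 | 0.530 | 0.382 |
| 25% | 0.000 | 0.510 | 0.356 |
| 30% | −0.200 | 0.412 | 0.227 |
| 35% | −0.400 | 0.314 | 0.098 |

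At a CV of 40% even the normal-theory 0.5th percentile is slightly negative (−0.03). A percentile read from the observed concentrations cannot be negative at any CV.

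**Step 2: can an analyte have a CV of 25% or more and still be judged normal?** I simulated Shapiro-Wilk at the 5% level, 400 runs per setting. The distributions are assumptions.

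- At n = 750, a normal variable restricted to positive values passed in 96–97% of runs at CVs of 25–35%, and in 74% at 40%. A near-symmetric, widely spread analyte therefore does reach the 4 SD branch.
- At n = 750, lognormal and gamma variables with a CV of 25% or more passed in no run. A clearly skewed analyte goes to the percentile branch.
- If normality were tested within subgroups, the screen would be weaker. The Discussion speaks of three age groups (750/3 = 250), and 3.2.1 adds a split by gender (250/2 = 125, assuming equal groups). A gamma variable with a CV of 30% passed in 8% of runs at n = 250 and 34% at n = 125. The article does not say at which level normality is tested.

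**Step 3: which rows depend on it.** For CPS and NAGSD, low citrulline is the only primary marker. For OTCD, raised ornithine remains. The other four low-marker rows use free carnitine or acylcarnitines, which 3.2 expects to be non-normal and hence on the percentile branch.

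**Step 4: how many low flags each limit gives.** One normal tail beyond 4 SD holds 0.0000317.

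- Among 750 controls: 750 × 0.0000317 ≈ 0.02, against 750 × 0.025 = 18.75 and 750 × 0.005 = 3.75.
- Among 1,500 screened children, if they resembled controls: 1,500 × 0.0000317 ≈ 0.05, against 1,500 × 0.025 = 37.5 and 1,500 × 0.005 = 7.5.

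**The case against.** The strongest reply is that the failure needs two things together, a passed normality test and a CV of at least 25%, and the documents show neither for citrulline. That stands: the finding is conditional, and below 25% the limit is positive, if low.

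A reader might go further and infer that every disorder with a low marker drops out, carnitine disorders included. The documents do not support that. Section 3.2 expects free carnitine and acylcarnitines to be non-normal, which gives them percentile limits. OTCD, CPT I, CPT II and CACT also have raised markers. CUD has more than one low marker, and all of them would have to be normal with a wide spread before it was lost. A reader might likewise infer that CPS and NAGSD will be reported with zero frequency. That too holds only under both conditions.

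A second reply is that a usable lower limit already exists in 3.2.1, that 2.3.1 points to the kit manual, and that 2.3.4 allows adjustment. This shows that a non-positive limit is not the only reading of the plan. It does not cancel the 4 SD sentence, which stands in the section that defines the diagnostic limits, and an open right to adjust is not a rule. It also means that the point overlaps with the conflict between the cut-off rules. It still adds something, because a sponsor could settle that conflict by keeping 4 SD, and the lower limit would then carry this weakness.

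A third reply is cost: moving a normal analyte from 4 SD to the 2.5th percentile raises the expected low-flag rate in healthy-like children about 790-fold (0.025/0.0000317). That stands and belongs in the decision.

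**Conclusion.** The concern holds in conditional form. The arithmetic is exact: as written, the lower 4 SD limit cannot flag anything for an analyte judged normal with a CV of 25% or more. At a CV of 20% it flags only values below 20% of the healthy mean. The practical exposure is citrulline, which means CPS and NAGSD on their only primary marker and OTCD on one of two. The carnitine-based rows (CUD, CPT I, CPT II, CACT) are exposed only if those analytes turn out normal, contrary to what 3.2 expects.

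The conclusion rests on an assumed CV, since none is given, and on citrulline passing the normality test. It should be corrected because the outcome would otherwise depend on a normality test and a spread that are not known in advance, and the correction is small.

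**What to change.** In 2.3.4, remove the mean − 4 SD limit for every marker shown with a down arrow in Table 3. For those markers, use the nonparametric lower percentile of the healthy group whatever the normality tests show. State one percentile and make 2.3.4, 3.2 and 3.2.1 agree on it (the 2.5th and the 0.5th both appear now). Say how that limit relates to the kit cut-offs in 2.3.1.

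This takes a few sentences and no new data. The cost is more low results to re-run and, if they persist, to confirm. Per marker, if screened children resembled controls, that is about 38 of 1,500 at the 2.5th percentile or about 8 at the 0.5th, against about 0.05 under 4 SD. The study limitations already name expensive testing as a constraint, so the choice of percentile should weigh this load. It should also weigh precision: the 0.5th percentile rests on about 4 of 750 controls and the 2.5th on about 19, with fewer in any age or gender subgroup.

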#### 2.3.5 Confirmatory tests

Patients will be immediately referred for confirmatory tests if the results exceed the thresholds. A reanalysis of the same sample will be performed if the results fall outside the threshold. Patients will be referred for confirmatory tests if the second test also falls outside the threshold.

Confirmatory tests include:

Clinical data; analysis of therapeutic effects; reanalysis LC-MS/MS; urine analysis for organic acids by gas chromatography-mass spectrometry (GC-MS); amino acid analysis; routine blood test; blood biochemistry; blood gas analysis; tests for glucose and ammonia in the blood; tests for homocysteine, lactate and pyruvate in the blood; tests for acetone in the urine; biotin, biotin enzyme profile; measurement of enzyme activity; tests for gene mutations; DNA analysis; magnetic resonance imaging of the brain and electroencephalography.

As known, gas chromatography-mass spectrometry is one of the best methods for diagnosing congenital acidemia. As organic acids are practically not reabsorbed in the renal tubules, their concentration in urine is higher than in the blood, and they are easier to determine in urine. Patients with a positive dry blood spot test result using TMS with or without clinical manifestations of IEM will have urine organic acids determined by gas chromatography-mass spectrometry.

To determine organic acids in urine using GC-MS, collecting 10–15 mL of morning urine in a clean, dry container without preservatives and transporting it in a thermos with food ice is necessary. The urine can be frozen and stored at a temperature of −20 C0 until analysis (Gallagher et al., 2018).

Before collecting urine, appropriate instructions regarding fluid intake, consumption of certain foods, avoidance of certain medications, etc., should be followed.

Several protocols have been developed for analyzing organic acids in urine samples in recent years. Typically, each of them includes five steps:1. Oximation by exposure to hydroxylamine. This step, although optional, is required to stabilize 2-keto acids, thus allowing a better recovery.2. Organic acids separation by liquid–liquid extraction.3. Trimethylsilyl (TMS) derivatization of the dried samples, obtained by adding BSTFA (N,Obis (trimethylsilyl)trifluoroacetamide): It is performed to improve the thermal stability and volatility of the organic acids.4. Injection into the GC/MS (Gas Chromatograph/Mass Spectrometer) apparatus. Scanning the resulting ions based on different mass/charge values allows a fragmentation profile (mass spectrum) to be constructed.5. Identification of mass spectra. The analysis is carried out on a tandem quadripole time-of-flight gas chromatograph—mass spectrometer “Agilent 7500 Q-TOF” to determine the concentration of the corresponding organic acid in urine according to the obtained mass spectrogram. The concentration of a specific organic acid in the urine is calculated as mmol/mol creatinine (in terms of normal creatinine) (Villani et al., 2017).

Identifying the affected individual has important implications for other family members, who may also require TMS dry blood spot testing, urine organic acid testing, and additional genetic testing.

Genetic counseling:

Aminoacidopathies, organic aciduria, and disorders of fatty acid metabolism are primarily inherited in an autosomal recessive manner. The parents are obligate heterozygotes; accordingly, each has one copy of the mutation that causes this disease. Heterozygous carriers have no symptoms of the disease. At conception, each sibling of the proband has a 25% risk of being affected, and in 50% of cases, being an asymptomatic carrier, a 25% chance that the child will not be sick and will not be a carrier. Unaffected siblings of affected individuals have a 2/3 chance of being heterozygotes.

DNA diagnostics. Next-Generation Sequencing:

Dried blood spots or whole blood can be used for whole exome sequencing. When using whole blood: collect 2–5 mL of the patient’s blood into tubes with EDTA preservative (purple cap); carefully invert the tubes several times to mix with the preservative, but do not shake to avoid hemolysis. Transport in a thermos with food ice can be frozen and stored at a temperature of - 80 C0. Whole blood must be delivered no later than 7 days after collection.

To conduct whole-exome sequencing of human DNA using NGS technology, sequencing platforms, a sequencer, an automatic station for DNA extraction, a fluorimeter, a centrifuge, a laminar flow cabinet, a flow-through bactericidal air recirculation, a fridge, nucleic acid quantitation instrument; nucleic acid quality analyzer; thermal cycler; vortex spot; ultrasonicator; standard laboratory supplies (pipettes, 96-well plates, centrifuge tubes) are needed.

This procedure is carried out by the institution’s approved standard operating procedures and the NGS protocol guidelines of the technology used and includes three stages:Stage I: Preparation of the library. Preparing the library consists of the following steps: DNA sample extraction, PCR amplification of DNA, and library cleaning.Stage II: Sequencing: reading the obtained information from the biochip and transferring the data to the software. Studies use the NovaSeq™ 6,000 Sequencing System (Illumina, Inc.).Stage III: Bioinformation analysis: a bioinformatic analysis of the obtained data and laboratory interpretation of the results are being carried out (Fernandez-Marmiesse et al., 2018; Marshall et al., 2020; Austin-Tse et al., 2022).

Table 3 presents the criteria for primary and repeated LC-MS/MS screening for IEM and confirmatory tests.

The tests will be conducted in the INVITRO laboratory (Kazakhstan, Almaty) by ICH E-6 Guidelines for Good Clinical Practice. The INVITRO laboratory is accredited to determine the profiles of acylcarnitines, succinylacetone, and amino acids by LS-MS/MS analysis by ISO 15189. From October 2022 to August 2024, the frequency of 37 AAD, OA, and FAOD will be assessed using LC-MS/MS technology in a group of children at high risk. A summary report on screening high-risk children for IEM in western Kazakhstan by LC-MS/MS will be presented.

## 3 Presenting the anticipated results

### 3.1 Study outcomes

The definition applied in the present study is as follows: Inborn errors of metabolism are inherited disorders caused by mutations in genes coding for proteins that function in metabolism. In particular: Amino Acids and Urea Cycle Disorders, Organic Acid Disorders, and Fatty Acid Oxidation Disorders.

Accordingly, we apply the following definitions of measured outcomes.

• Primary outcomes:1. Normal and abnormal values of amino acids, acylcarnitines, and succinylacetone in dry blood spots of newborns and children of different age groups measured in µmol/L through liquid chromatography-tandem mass spectrometry (LC-MS/MS).

Metabolites to be measured:

Amino acids: Alanine (Ala), Arginine (Arg), Citrulline (Cit), Glutamine (Gln), Glutamic acid (Glu), Glycine (Gly), Leucine (Leu), Isoleucine (Ile), Hydroxyproline (Pro-OH), Methionine (Met), Ornithine (Orn), Phenylalanine (Phe), Proline (Pro), Tyrosine (Tyr), Valine (Val). Acylcarnitines: Free carnitine (C0), Acetylcarnitine (C2), Propionylcarnitine (C3), Malonylcarnitine+3-Hydroxybutyrylcarnitine (C3DC/C4OH), Butyrylcarnitine (C4), 2H9-C5-Methylmalonylcarnitine+3-Hydroxyisovalerylcarnitine (C4DC/C5OH), Isovalerylcarnitine (C5), Tiglylcarnitine (C5:1), Glutarylcarnitine (C5DC), Hexanoylcarnitine (C6), Octanoylcarnitine (C8), Octenoylcarnitine (C8:1), Decanoylcarnitine (C10), Decenoylcarnitine (C10:1), Decadienoylcarnitine (C10:2), Dodecanoylcarnitine (C12), Hydroxydodecenoylcarnitine (C12:1), Myristoylcarnitine (C14), Tetradecenoylcarnitine (C14:1), Tetradecadienyl-carnitine (C14:2), Hydroxytetradecanoylcarnitine (C14OH), Palmitoylcarnitine (C16), Hexadecenoylcarnitine (C16:1), 2H3-C16-3-Hydroxy-Hexadecanoylcarnitine (C16OH), 2H3-C16-3-Hydroxypalmitoleylcarnitine (C16:1OH), 2H3-Stearoylcarnitin (C18), 2H3-C18-Octadecenoylcarnitine (C18:1), 2H3-C18-Linoleylcarnitine (C18:2), 2H3-C18-3-Hydroxystearoylcarnitine (C18OH), 2H3-C18-3-Hydroxyoleoylcarnitine (C18:1OH), 2H3-C18-3-Hydroxylinoleoylcarnitine (C18:2OH). Succinylacetone (SUAC) (13C5-MPP IS).2. The number and proportion of children with detected abnormal metabolite values and checked by retesting and/or confirmatory tests if the results exceeded the thresholds.

• Surrogate endpoints:1. Abnormal values of organic acids in urine measured through gas chromatography-mass spectrometry (GC-MS) applied for confirmatory tests.2. Abnormal values of any other tests, such as tests for glucose and ammonia in the blood; tests for homocysteine, lactate, and pyruvate in the blood; tests for acetone in the urine; biotin, biotin enzyme profile; measurement of enzyme activities; tests for gene mutations; DNA analysis; magnetic resonance imaging of the brain and electroencephalography.3. The number, combination, and severity of clinical symptoms in high-risk children confirmed by the pediatricians’ examination.

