#### 2.3.2 Specimen preparation and LC-MS/MS analysis

The Neobase2 TM Non-derivatized MSMS kit (PerkinElmer, Wallac Oy, Turku, Finland) is used to quantify 15 amino acids, free carnitine, 35 acylcarnitines, and succinylacetone in dried blood spots according to the manufacturer’s instructions.

The vial with lyophilized isotope-labeled internal standards (IS) is recovered by adding 1.4 mL of the extraction solution that is included in the Neobase 2 kit. The Extraction Working Solution (EWS) IS prepared by diluting the recovered internal standards with the extraction solution 1:100 (v/v) and 1: 50 (v/v) for SUAC.

Dried blood samples are analyzed using Shimadzu LCMS-8050 Triple Quadrupole Mass Spectrometer (Shimadzu Corporation, Kyoto, Japan). Level I and Level II (low standard and high standard) dried blood drops are included in each assay lot of the Neobase2 TM Non-derivatized MSMS kit to monitor system accuracy and precision.

To analyze amino acids, acylcarnitines, and succinylacetone, stored DBS card samples must be brought to room temperature (+18 to +25°C) before extraction. A 3.2 mm disc (equivalent to ∼3.1 µL of whole blood) is punched out of one dried blood spot with a diameter of 3.2 mm using a Wallac DBS Puncher (PerkinElmer, Wallac Oy, [name]) into the well of the 96-well polystyrene U-bottom microplate supplied with the Neobase2 TM Non-derivatized MSMS kit. After adding 125 μL of working extraction solution to each well of the microplate, the plate is covered with an adhesive aluminum film and incubated for 30 min at room temperature on a microplate shaker with a shaking speed of 650 rpm. After incubation, 100 μL of the supernatant is transferred to a new 96-well U-bottom microplate, covered with aluminum foil to reduce evaporation and incubated for 1 h. Then, the plate is placed into the Shimadzu LCMS-8050 Triple Quadrupole Mass Spectrometer autosampler, and 5 μL of supernatant is injected into the LCMS for analysis.

Liquid chromatograph-mass spectrometer Shimadzu LCMS-8050 (Shimadzu Corporation, Japan) used for MS/MS analysis is equipped with a binary pump, an autosampler, and an electrospray ionization source (ESI). Samples are introduced into the LC-MS/MS system through an ESI source for atmospheric pressure ionization, and analysis of the samples is performed using electrospray ionization flow analysis and tandem mass spectrometry (FIA-ESI-MS/MS).

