#### 2.3.3 Data acquisition and processing

A program for the LC-MS/MS solvent pump (included) is being set to deliver a mobile phase at a constant flow rate of 150 *μ*L/min, and data are collected in Positive Ion Multiple Reaction Monitoring (MRM) mode. LC-MS/MS ionization source parameters: interface voltage 4.5 kV, interface temperature 250°C, dissolution line temperature 250°C, heating block temperature 400°C, atomizing gas flow 3.0 L/min, and drying gas flow 15.0 L/min. Argon is used at a pressure of 230 kPa as a collision gas. Lab Solution software (version 5.82 SP1, Shimadzu Corporation, Kyoto, Japan) is applied for data collection. Amino acid and acylcarnitine levels will be automatically calculated according to the set internal standards using the Neonatal Solution software (version 2.20, Shimadzu Corporation, Kyoto, Japan). The total running time for each sample is 1.5 min; data is recorded within 0.9 min. The quality control samples supplied with the Neobase2 TM Non-derivatized MSMS kit are extracted and analyzed in parallel with the samples of healthy controls and patients to check the reliability of the data generated by the LC-MS/MS analysis.

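### Leucine, isoleucine and hydroxyproline are planned as three separate analytes, but the assay as described gives them one shared signal, so separate reference intervals and the Leu/Ile screening ratio are not supported

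*Protocol article*

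**What the plan says.** Primary outcome 1 (protocol article, section 3.1) is the normal and abnormal values of a named list of metabolites in dried blood spots, in µmol/L. The amino acids in that list include "Leucine (Leu), Isoleucine (Ile), Hydroxyproline (Pro-OH), Methionine (Met", each as its own entry. Section 3.2.1 promises descriptive statistics and reference intervals for 15 amino acids, percentile cut-offs for every analyte, and cut-offs for the analytes and ratios of Table 3. Section 5 makes reference values the subject of the first results paper.

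The assay is set out in sections 2.3.2 and 2.3.3:

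- A non-derivatized kit "is used to quantify 15 amino acids, free carnitine, 35 acylcarnitines, and succinylacetone in dried blood spots".
- The instrument: "Dried blood samples are analyzed using Shimadzu LCMS-8050 Triple Quadrupole Mass Spectrometer".
- Sample introduction: "analysis of the samples is performed using electrospray ionization flow analysis and tandem mass spectrometry (FIA-ESI-MS/MS".
- Acquisition at constant flow, where "data are collected in Positive Ion Multiple Reaction Monitoring (MRM) mode".
- Timing: "The total running time for each sample is 1.5 min; data is recorded within 0.9 min".

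The equipment named is a pump, an autosampler and an electrospray source. No column, gradient or list of transitions is given.

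In Table 3 (section 2.3.4), the MSUD cell for primary and repeated screening lists raised Val, Ile and Leu, and the ratios Leu/Ile, Leu/Phe, Xle/Ala, Xle/Phe and Val/Phe. The confirmatory cell of the same row lists "Val, Leu/Ile, Leu/Phe ratio (Blood".

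**The concern.** Flow injection does not separate compounds in time before they reach the mass spectrometer, so analytes are told apart only by mass and fragment. Leu and Ile are isomers, and Pro-OH shares their nominal mass. If all three are read in one channel, the plan promises three reference intervals for a single quantity, and one MSUD screening ratio has no separate numerator and denominator.

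Reference values are a primary outcome and the first planned paper. Section 3.2.1 also intends to compare them with other populations. A pooled value published as leucine would be set against a different quantity wherever the other study had separated the isomers.

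The protocol's own notation points the same way. Xle, the symbol for leucine and isoleucine not distinguished, stands in the same Table 3 cell as Leu/Ile. Section 3.1 also merges other same-mass pairs into one entry, such as "Malonylcarnitine+3-Hydroxybutyrylcarnitine (C3DC/C4OH", but does not do so here.

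**Working it through.** **Inputs.** The analyte list is from section 3.1, the assay from sections 2.3.2 and 2.3.3, and the MSUD ratios from Table 3. The molecular formulas and atomic masses are not in the document and are taken as standard chemistry: Leu and Ile C6H13NO2, Pro-OH C5H9NO3. Unit-mass selection on the triple quadrupole is an assumption.

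**1. The stated count of amino acids.** Section 3.1 names Ala, Arg, Cit, Gln, Glu, Gly, Leu, Ile, Pro-OH, Met, Orn, Phe, Pro, Tyr and Val. That is 15, as stated, but only if Leu, Ile and Pro-OH count as three.

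**2. Can mass alone separate them?** Protonated masses [M+H]+:

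| Analyte | [M+H]+ | After loss of HCOOH |
|---|---|---|
| Leu | 132.1019 | 86.0964 |
| Ile | 132.1019 | 86.0964 |
| Pro-OH | 132.0655 | 86.0600 |

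- Leu and Ile differ by 0, so no mass resolution separates the intact ions.
- Pro-OH differs by 132.1019 − 132.0655 = 0.0364. The resolving power needed is 132.1019 / 0.0364 ≈ 3,600, which unit-mass selection does not give.
- After the loss of HCOOH all three are still at nominal 86.

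With this common fragment and no separation in time, all three fall in the one channel 132 > 86.

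**3. Amino-acid signals after merging.** 15 − 3 + 1 = 13.

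**4. MSUD screening ratios.** Five are listed: Leu/Ile, Leu/Phe, Xle/Ala, Xle/Phe and Val/Phe. With one pooled signal, Leu/Ile cannot be formed and Leu/Phe is the same quantity as Xle/Phe. Three distinct ratios remain: Xle/Ala, Xle/Phe and Val/Phe.

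**5. The metabolite total.** The stated total is 15 + 35 + 1 = 51. Section 2.3.2, read literally, counts free carnitine in addition: 15 + 1 + 35 + 1 = 52. Section 3.1 names 15 amino acids, 31 carnitine entries (C0 included) and succinylacetone: 15 + 31 + 1 = 47. After merging: 13 + 31 + 1 = 45.

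**The case against.** The strongest reply is that the transitions are not shown. Acquisition is by multiple reaction monitoring, which selects on the fragment as well as the precursor, and section 2.3.2 defers to the manufacturer's instructions. A journal article may reasonably leave transitions to the full method. A fragment specific to one isomer, or one that distinguishes Pro-OH with its different formula, would change the conclusion. This stands: a reader might infer that separate values are impossible, but the document supports only that the method as described does not provide them.

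Other parts of the reply also hold:

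- Leu/Ile is not among the nine ratios that the text of section 2.3.4 says will be set. It enters through Table 3 and the general undertaking in section 3.2.1 to give cut-offs for that table.
- The confirmatory entry "Val, Leu/Ile, Leu/Phe ratio (Blood" is no evidence of a fault at screening. Section 2.3.1 plans plasma amino acid analysis for confirmation, and another method may separate Leu from Ile there.
- Three distinct MSUD ratios, raised Val and the pooled signal remain at screening, so no loss of MSUD detection is shown.
- The amino acids run in near-alphabetical order except for this trio, which sits together between Gly and Met. That fits one combined entry written out as three.

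The last point explains how the list may have arisen but does not remove the contradiction. The count of 15, the interval for each analyte and the Leu/Ile screening entry all depend on reading the trio as three measurements.

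**Conclusion.** The point holds in conditional form. By the assay as described, Leu, Ile and Pro-OH share one signal. Separate intervals for them and the first-tier Leu/Ile ratio are then not derivable. Three of the 15 listed amino acids become one signal, leaving 13, and the five MSUD screening ratios reduce to three distinct ones. This rests on unit-mass selection, the common fragment, and the absence of any separating transition or step that the document leaves unmentioned.

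Three stronger inferences are not supported:

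- A reader might subtract two from the stated total and report 49 metabolites. The section 3.1 list does not reach 51 to begin with; it gives 47, or 45 after merging.
- A reader might expect a combined analyte to remove false positives caused by raised Pro-OH. If the signal is shared, renaming it leaves the Pro-OH contribution where it was.
- A reader might conclude that Leu/Ile would be reported as 1.0 for every child. That would follow only if the laboratory reported one channel under both names, which the document does not say.

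Sample size and the detection-rate formula are untouched. The matter concerns what the reference-value paper can report and how the MSUD screening entry is defined.

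**What to change.** Reconcile sections 2.3.2, 2.3.4 (Table 3), 3.1 and 3.2.1 in one of two ways.

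1. **Report one analyte.** Replace the three entries in section 3.1 with Leu+Ile+Pro-OH (Xle) and set one reference interval for it. In the MSUD screening cell of Table 3, use Xle throughout: Xle, Val, Xle/Phe, Xle/Ala and Val/Phe, without Leu/Ile. Keep separate Leu and Ile only for the confirmatory amino acid analysis. Restate the amino-acid count as 13 wherever 15 appears.
2. **Keep three analytes.** Name in section 2.3.2 or 2.3.3 the transition or separation step that resolves them.

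Either way, recount the metabolite total against the section 3.1 list and make the totals agree throughout.

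The first option costs a rewording of the outcome list, one table row and the counts, with no new samples or assays. The second costs a sentence if a resolving transition is already in use. If it is not, the assay itself would have to change, at a cost the document does not allow one to judge. The change is best made before the reference-value paper fixes the intervals.
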